| Efficacy Assessment | 
1. Data Collection
 
1) Questionnaire
 
 
- Patients and guardians in both the intervention and control groups will complete a questionnaire at the time of participant registration.
 
- Participants in the intervention and control groups will complete a follow-up questionnaire 3 months after registration.
 
- Participants in the intervention group will complete an additional questionnaire 6 months after registration. In the case of the control group, only those who will provide consent to participate in the additional questionnaire at 3 months will complete the additional questionnaire at 6 months.
 
 
2) Medical Records Investigation
 
 
- Medical records at medical institutions will be investigated at 3, 6, and 12 months after the patient's registration for hospitalization (number and dates of hospitalizations), critical care use (date of ICU admission, date of ventilator support, and number of CPR attempts), and emergency room use (number of emergency room visits) at each time point.
 
- In the case of death at 3, 6, and 12 months after registration, the deceased patient's use of medical services (hospitalization, critical care use, and emergency room use) within one month of their death will be investigated.
 
 
3) Secondary Data Linkage
 
 
- For patients who will provide consent to secondary data linkages, the hospitalizations, medical expenses, death, type of end-of-life medical services used, and the use of emergency room, critical care, and hospice between the time of registration and 12 months will be investigated when all patients have been enrolled for 12 months or longer.
 
- Death, information related to hospice use, and the type of end-of-life medical services used will be investigated when all patients have been enrolled for 18 months or longer.
 
- For patients who will consent to secondary data linkages, whether legal forms for life-sustaining treatments (e.g., advance directives and physician orders for life-sustaining treatment) have been completed and by whom will be investigated at 12 and 18 months of enrollment when all patients have been enrolled for 12 and 18 months or longer, respectively.
 
 |

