## B. Medical Record Investigation

- A research nurse will investigate the medical history (e.g., diabetes, hypertension, hyperlipidemia, heart disease, stroke, cerebral hemorrhage, chronic liver disease, chronic kidney disease, asthma, chronic obstructive pulmonary disease, musculoskeletal disease, digestive disease, neurological disease, and psychiatric disease), cancer diagnosis (e.g., carcinoma ICD-10 code and date of diagnosis), cancer treatment history, and plan for life-sustaining treatment at the respective medical institution at the time of patient registration.
- A research nurse will conduct the medical record survey of the respective medical institution at

3, 6, and 12 months of patient enrollment to investigate the status of cancer treatment, hospitalization, ER use, and the use of medical services by the severely ill patient from the time of the previous assessment to each time point, as well as the use of medical services one month prior to death in the case of a deceased patient. The following items will be investigated through medical record surveys.

|                                                                                                                                                                                                                                     | 3 Months | 6 Months | 12 Months |
|-------------------------------------------------------------------------------------------------------------------------------------------------------------------------------------------------------------------------------------|----------|----------|-----------|
| Cancer Treatment Status
Cancer Progression
Anti-cancer Treatment Plan
Other Treatment Plans                                                                                                                                | O        | O        | O         |
| Hospitalization at a Medical Institution
Date of Hospitalization and Discharge
Hospitalization Route (e.g., outpatient or ER)
Scheduled Hospitalization
Result of Hospitalization (e.g., discharge, transfer, or death) | O        | O        | O         |
| Use of the ER
Date of Use (month and year)
KTAS at the ER
ER Address
Result of the Use (e.g., discharge, transfer, or death)                                                                                            | O        | O        | O         |

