| Critical Care Use
Date of ICU Admission
Date of Ventilator Support
Number of Cardiopulmonary Resuscitations                                                                                                                | O        | O        | O         |
| Death in Hospital
Date of Death
Place of Death (e.g., ward, ICU, or ER)
Cause of Death (based on the death certificate)                                                                                                    | O        | O        | O         |
| Medical Service Use 1 Month Before Death
Date of ICU Admission
Date of Ventilator Support
Number of Cardiopulmonary Resuscitations
Undergoing Anti-cancer Treatment                                                     | O        | O        | O         |

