### Secondary data linkage plan for primary and secondary outcomes

| Item                                                     | Outcome measurement timing (from the time of enrollment) |          |           |           |
|----------------------------------------------------------|----------------------------------------------------------|----------|-----------|-----------|
|                                                          | 3 months                                                 | 6 months | 12 months | 18 months |
| Hospitalization                            |                                                          |          |           |           |
| Hospitalization date, discharge date                     | ○                                                        | ○        | ○         |           |
| Hospitalization route (outpatient or emergency room)     |                                                          |          |           |           |
| Hospitalization results (discharge or death)             |                                                          |          |           |           |
| Emergency room use                         |                                                          |          |           |           |
| Date (year, month, and date)                             | ○                                                        | ○        | ○         |           |
| Result (discharge, hospitalization, or death)            |                                                          |          |           |           |
| Critical care use                          |                                                          |          |           |           |
| Date of ICU hospitalization (day)                        | ○                                                        | ○        | ○         | ○         |
| Date of ventilator support (day)                         |                                                          |          |           |           |
| Number of CPR attempts                                   |                                                          |          |           |           |
| Hospice use                                |                                                          |          |           |           |

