#### *2) Secondary Efficacy Endpoint*

- Domain 1: The secondary endpoints related to patients' use of medical services and critical care are described below.
  - Number of unscheduled hospitalizations within 6 months of study enrollment (continuous or count variable)
  - Length of hospitalization (total length of hospitalization; continuous variable)
  - History of hospitalization (dichotomous variable)
  - Number of ER visits (continuous variable)
  - Length of ICU hospitalization (total length of hospitalization; continuous variable)
- Domain 2: The secondary endpoints related to patients' quality of life and their satisfaction with the service are described below.
  - Patient's quality of life (EQ-5D; continuous variable)
  - Patient's degree of symptom control (ESAS; continuous variable)
  - Patient's emotional status (PHQ-9; continuous variable)

- Patient's satisfaction with the service (continuous variable)
  
- Domain 3: The secondary endpoints related to the patient's death and preparation of advanced directives are described below.
  - Survival after enrollment (days; continuous variable)
  - Length of ICU hospitalization within 1 month of the patient's death (total length of hospitalization; continuous variable)
  - History of anti-cancer treatment within 1 month of the patient's death (dichotomous variable)
  - Duration of ventilator support within 1 month of the patient's death (total number of days; continuous variable)
  - Preparation of advance directives or physician orders for life-sustaining treatment (dichotomous variable)
  
- Domain 4: The secondary endpoints related to guardians' quality of life and their satisfaction with the service are described below.
  - Guardian's quality of life (EQ-5D; continuous variable)
  - Guardian's emotional status (PHQ-9; continuous variable)
  - Guardian's burden of care (CRA\_K; continuous variable)
  - Guardian's care competency (continuous variable)
  - Guardian's satisfaction with the service (continuous variable)
  
- Domain 5: The secondary endpoints related to medical expenses are described below.
  - Direct medical expenses (continuous variable; KRW)
  - Indirect medical expenses (continuous variable; KRW)

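### The chart-review list gives critical care start dates but no end dates or day counts, so it does not support three secondary endpoints defined as ICU or ventilator durations

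*Protocol*

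**What the plan says.** **Endpoints.** Section 12.A.2 defines three critical care endpoints as continuous durations. Domain 1 has "Length of ICU hospitalization (total length of hospitalization; continuous variable"). Domain 3 has the ICU length within 1 month of death, and "Duration of ventilator support within 1 month of the patient's death (total number of days; continuous variable"). Section 12.B.2 compares the arms on means, and Section 12.C.2 reads a difference at the 0.05 level as evidence that the intervention worked on that endpoint.

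**Chart review.** The Overview (Efficacy Assessment, Medical Records Investigation) lists "critical care use (date of ICU admission, date of ventilator support, and number of CPR attempts"). The table in Section 11.B, introduced as the list of what the survey will examine, gives "Date of ICU Admission Date of Ventilator Support" under critical care use and names the same two items again for the month before death. For ordinary admissions that table asks for "Date of Hospitalization and Discharge". It also records the date and place of in-hospital death, with ICU as one of the places.

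**Linkage.** The linkage plan in Section 11.C lists "Date of ICU hospitalization (day") and "Date of ventilator support (day"), at 3, 6, 12 and 18 months.

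**The concern.** A length needs a start and an end, or a count of days. For critical care the chart list supplies only a start for the ICU, and one undefined date item for the ventilator. This is a matter of data collection, so a later analysis plan cannot repair it: no derivation rule recreates an end date that was not recorded.

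Two things are at stake. Without a recorded end, whoever builds the dataset must choose a substitute or leave the value missing, and the protocol does not say which. And if the linked claims fill the gap for only some patients, or mainly for one arm, a difference in means may reflect the source of the data as well as the care given.

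**Working it through.** The protocol gives no figure to reproduce. The check sets the endpoints against the items collected.

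**1. Chart review (Section 11.B), the source described for both arms without a linkage-consent condition**

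| Episode | Start named | End or day count named |
|---|---|---|
| Ordinary hospital stay | yes | yes, discharge date |
| ICU stay | yes, admission date | no |
| Ventilator support | a date, not defined as start or as each day | no |
| In-hospital death | not applicable | date and place of death |

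The table names both ends of an ordinary stay but not of an ICU stay, so the gap is specific to critical care.

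**2. Which endpoints the chart items support**

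- Total ICU length: derivable only if the stay ends in ICU death, where the date of death closes it.
- ICU length within 1 month of death: the same. A patient who left the ICU before dying has no end date for that stay.
- Ventilator days within 1 month of death: not derivable from the item as worded. Death in the ICU does not show when ventilation stopped.

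**3. What the gap means for one record (assumed dates, not trial data).** Take hospital admission on day 1, ICU admission on day 5 and hospital discharge on day 20. The listed items bound the ICU stay only between 0 and 20 − 5 = 15 days. If the patient instead stayed in the ICU until dying there on day 20, the stay is fixed at 15 days.

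**4. Whether linkage closes the gap**

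- *Meaning.* The ICU and ventilator items carry the label 'day', while the emergency room date in the same table is spelled out as year, month and date. The contrast suggests that 'day' means days of use. The table does not say so.
- *Consent.* Section 9.A.1 makes linkage depend on a separate box on the consent form. The protocol gives no expected consent rate.
- *Arms.* Section 11.C opens by wording linkage for consenting patients in the intervention group. Its later sentence, on 18-month data, speaks of the intervention study, which could mean both arms. The Overview sets no arm limit. On the narrow reading, control patients have only the chart items.

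**5. Extent.** Section 12.A.2 lists 5 + 4 + 5 + 5 + 2 = 21 secondary endpoints across Domains 1 to 5. Three are affected.

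**The case against.** The strongest reply is that a protocol list names topics, and individual fields belong to the case report form, which is not shown. The Overview is clearly shorthand: it does not spell out discharge dates for ordinary stays either, though Section 11.B does. The linkage table probably supplies day counts, 'date of ventilator support' could mean every date of support, and the research nurse can return to the same charts.

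Much of this stands. The Overview alone proves little, so the argument rests on the Section 11.B table, which does name discharge for ordinary stays and so does not read as uniform shorthand. The case report form may hold more, but the protocol's own list does not support its own endpoints. The linkage reading is plausible but undefined, and it leaves the questions of consent and arm open.

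A reader might go further and infer that these endpoints cannot be derived at all, or that ICU stays will be overstated because hospital discharge will stand in for ICU discharge. The documents support neither. ICU deaths have an end date, linkage may supply days, and nothing in the protocol uses hospital discharge as the end of an ICU stay. Any multiple by which stays would be inflated would come from an invented record.

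**Conclusion.** The point holds in a limited form. As listed, the chart items do not yield total ICU length, ICU length within 1 month of death, or ventilator days within 1 month of death, apart from ICU stays that end in ICU death. Linkage may fill the gap, but its term is undefined, it needs separate consent, and one passage words it for the intervention group, so a common source for both arms is not assured.

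The size of any resulting error cannot be stated. The protocol gives neither the frequency of critical care use nor the linkage consent rate, and it names no substitute end date. The conclusion assumes that the Section 11.B list is what will be collected. If the case report form already holds end dates or day counts in both arms, what remains is to align the protocol text with it. The primary endpoint, the sample size and the other 18 secondary endpoints are untouched. The change is still worth making, because a missing end date cannot be restored at the analysis stage.

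**What to change.** - In the Overview's medical record items and in the Section 11.B table (critical care use, and the month before death), record ICU admission and discharge dates and ventilator start and stop dates, or day counts, for each episode, in both arms.
- In the linkage table, state that 'day' means the number of days of use. In Section 11.C, state which arms linkage covers, so that it agrees with the Overview.
- In Section 12.A.2, define each endpoint as the sum of episode days falling inside its window, taken from the same source in both arms.
- If end dates prove unrecoverable, replace the length by any ICU or ventilator use (yes/no) for the whole endpoint in all patients. Switching patient by patient would mix two scales according to who has missing data.

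The cost is two extra date fields per episode on a form that the research nurse already completes from the same charts at 3, 6 and 12 months, plus a return to the charts for patients already surveyed. Sample size and the primary analysis do not change.

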| Study Design                                                   | Korean multicenter non-randomized cluster clinical trial                                                                                                                                                                                                                                                                                                                                                                                                                                                                                                                                                                                                                                                                                                                                                                                                                                                                                                                                                                                                                                    |
| Study Period                                                   | Date of IRB approval – December 31, 2026                                                                                                                                                                                                                                                                                                                                                                                                                                                                                                                                                                                                                                                                                                                                                                                                                                                                                                                                                                                                                                                    |

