| Statistical Analysis         | 
The HBMC intervention group, control group, and each participating institution will be set as analysis groups for the statistical analysis of the outcome variables.
 
The analysis groups of the participants are based on the group assignment according to the initial intention-to-treat (ITT) that relies solely on the intervention of the original assignment to estimate the effectiveness in the intervention group conservatively. In the case of withdrawal of consent or dropout during follow-up, data collected till the time of withdrawal or dropout will be used. A comparative analysis of the dropout rate between the two groups will be performed and reported.
 
 
- Descriptive analysis of underlying characteristics
 
 
Continuous variables: mean (standard deviation) and median (IQR)
 
Dichotomous variables: frequency (%)
 
 
- Analysis of between-group differences
 
 
An analysis will be performed using a regression model while considering that participants, the observation units, were clustered into six participating institutions to evaluate the effects of the HBMC intervention and correcting for the differences in the baseline characteristics between the groups.
 
Dichotomous variable (primary endpoint): A generalized estimation equation (GEE) will be used to analyze the clusters of patients in participating institutions, and the effects of the HBMC intervention will be evaluated using a logistic regression model based on the logit link function.
 
Continuous variables: The effects of the HBMC intervention will be evaluated using a mixed model to consider the patient clusters in the participating institutions.
 
Count data: A GEE will be used to consider the patient clusters in the participating institutions, and the effects of the HBMC intervention will be evaluated using a regression model that appropriately uses Poisson and negative binomial as random components according to the distribution of variables using the logit link function as the link function.
 |

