## **6. Sample size calculation**

The number of samples for the home-based program required in this study is based on a dichotomous variable, which is the primary endpoint, to secure enough patients for a stable and sufficient power. The primary endpoint of this study is the unplanned hospitalization within six months following enrollment. This study aims to determine the differences in the effects by comparing the odds ratio based on the proportion of unplanned hospitalizations in the intervention and control groups. Although no previous intervention study with a similar design has been conducted outside of Korea, the difference in pre- and post-intervention changes between the intervention and control groups should be approximately 20% (20% less in the intervention group) based on the literature review. The number of institutions in both groups is three. The parameters will be estimated using a generalized estimation equation (GEE) to compensate for the cluster effects of the study participants. The comparisons between the two groups will be analyzed using a logistic regression model, which is used to compare the effects of dichotomous outcome variables while considering other confounding variables. Therefore, a power of 80%, a significance level of 0.05 to control for type 1 error, and a 20% difference in the number of unplanned hospitalizations by intervention was used to calculate the sample size. For a ratio of 1:1 for participants in each group, the minimal sample size should be 396 patients

in total, including 198 patients for three clusters in the intervention groups and 198 patients for three clusters in the control group (assuming within-cluster coefficient=0.015).

Within-cluster coefficient (Intraclass correlation coefficient, ICC) was estimated using the analysis of variance (ANOVA) estimation method according to similar previous studies. The calculation formula is as follows (Sheng et al., 2012; Chen et al., 2015)

In the formula, 
$$n_A = \frac{1}{k-1}(N - \sum n_i^2/N) \quad MSB = \frac{1}{k-1}(\sum Z_i^2/n_i - (\sum Z_i)^2/N)$$

$$MSW = \frac{1}{N-k}(\sum Z_i - \sum Z_i^2/n_i)$$
  $k$  is the number of cluster and  $N$  is the total number of study participants.  $n_i$  and  $Z_i$  are the number of participants in group  $i$  and number of patients with endpoints in group  $i$ , respectively. Incidence rates by group were extracted from a study by Chen et al. (2015) and applied in the present study.

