### ***2) Secondary Efficacy Endpoint***

- For each item in Domains 1 through 5, the means of continuous variables of the intervention and control groups will be compared. Additionally, the proportions of dichotomous variables of the intervention and control groups will be compared.
- Post-enrollment duration of survival in the intervention and control groups will be compared using the Kaplan-Meier curve.

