### ***4) Statistical analysis***

Definition of home-based medical service intervention group and study dropouts: Patients who provided informed consent to the selected home-based medical service intervention institutions and control group institutions are defined as the intervention group and control group, respectively. Based on the principle of group classification by intention-to-treat (ITT) that only considers the initial classification of intervention, omission of home-based medical service is still defined as the intervention group, which causes a bias that reduces the effects in the treatment group. Despite the study's design to conservatively estimate the effects in the treatment group, if significant differences are observed in the results among patients who withdraw consent or dropout during follow-up, data up to the point of withdrawal of consent or dropout will be used. Dropout rates will be analyzed and reported for each group.

The mean proportion of unplanned hospitalization will be compared between the intervention and control groups for the primary outcome. The mean of continuous variables and a fraction of dichotomous variables for each item in domains one to five will be compared between the two groups for the secondary outcome. A generalized estimation equation will be used to evaluate intra-group correlations to compensate for clusters of patients in the participating institutions. Survival after enrollment will be compared using the Kaplan-Meier curve and Cox proportional hazard model.

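### The synopsis commits to baseline adjustment, but the body's evaluation and analysis sections describe only unadjusted comparisons in a non-randomised trial of three versus three hospitals

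*Protocol*

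**What the plan says.** The overview describes a "Korean multicenter non-randomized cluster clinical trial", with three named hospitals in each arm.

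Adjustment is mentioned in two places:

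- **Overview, Statistical Analysis row.** The between-group regression allows for the six institutions while "correcting for the differences in the baseline characteristics between the groups". The sentence comes before the paragraphs on dichotomous, continuous and count outcomes, so it covers all three. It names no covariate and gives no rule for choosing one.
- **Section 6 (sample size).** The logistic model is said to compare the groups "while considering other confounding variables". Again no variable is named.

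It is not mentioned in the sections that set out evaluation and analysis:

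- **Section 12.B.** The primary comparison is of mean proportions. For secondary endpoints, "the means of continuous variables of the intervention and control groups will be compared", and proportions likewise.
- **Section 12.C.** The primary result is read from a 20% difference in group means.
- **Section 14.B.4.** "The mean proportion of unplanned hospitalization will be compared between the intervention and control groups for the primary outcome". GEE is brought in to handle the grouping of patients within institutions, and Kaplan-Meier and Cox methods are named for survival. No covariate or confounder appears.

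**The concern.** In a randomised trial, silence on covariates costs mainly precision. Here the arms are two sets of hospitals, and nothing in the design balances their patients: no matching, stratification or weighting is described. One difference is even written in. The overview waives the home-visit distance exclusion for the control group, whereas section 5.B states that exclusion without the waiver. Covariate adjustment is therefore the only protection against case-mix confounding that the protocol mentions, and section 14.B.4 does not carry it.

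Two analysts, one working from the overview and one from section 14.B.4, could report different primary odds ratios and both claim to have followed the protocol. The overview's wording is also loose. Its most natural reading is adjustment for the differences that are seen, which leaves the covariate set open until the data are in and can pass over a strong prognostic factor with a modest imbalance.

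**Working it through.** **1. The plan's own power figure.** Section 6 uses "a power of 80%, a significance level of 0.05 to control for type 1 error", 198 patients per arm in three clusters of 66, ICC 0.015 and an effect size of 0.2. The control rate and the sidedness are not stated; I assume two-sided.

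- Design effect = 1 + (66 − 1) × 0.015 = 1.975.
- Effective n per arm = 198 / 1.975 = 100.3.
- With assumed rates of 50% and 30%, power = Φ[(0.20 − 1.96 × √(2 × 0.40 × 0.60 / 100.3)) / √((0.25 + 0.21) / 100.3)] = Φ(0.95) = 0.829. The section 6 table gives 0.83007.

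The figure reproduces as a plain two-proportion comparison with a design effect. It contains no covariate term, so nothing below changes the sample size.

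**2. Illustrative bias in an unadjusted contrast.** Assumptions, none from the documents: event risk 60% at ECOG 2 and 40% at ECOG 1, an average ECOG 2 share of 50%, and no true effect.

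- Bias = risk gap × difference in ECOG 2 share.
- 20-point difference: 0.20 × 0.20 = 0.04.
- 40-point difference: 0.20 × 0.40 = 0.08.
- SE of the risk difference = √(2 × 0.50 × 0.50 / 100.3) = 0.0706.
- Standardised bias = 0.04 / 0.0706 = 0.57 and 0.08 / 0.0706 = 1.13.
- Rejection rate of a nominal 5% test: about 9% and about 20%.

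**3. Other assumed values.** One binary prognostic factor with odds ratio 1.5 to 3, an imbalance of 10 to 30 points, base risk 20% to 40%, and the same effective n. With no true effect, the spurious odds ratio runs from 0.96 to 0.73 and the rejection rate from 5% to 21%. The direction of a real imbalance is unknown; it could as easily hide an effect as create one.

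**4. How much each weakness matters.** Simplified simulation: continuous outcome, no clustering, 100 per arm, no true effect, assumed imbalance 0.3 SD, assumed correlation 0.5 between covariate and outcome.

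| Analysis | Type I error |
|---|---|
| Unadjusted | 18.4% |
| Adjusted only if the baseline difference is significant | 6.6% |
| Always adjusted | 5.2% |

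Omitting adjustment is the larger problem; choosing covariates by observed difference is a smaller one.

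**5. Questionnaire outcomes.** Adjusting for an enrolment score with correlation r to the follow-up score removes a share r² of the patient-level variance: 0.5² = 25% and 0.7² = 49% (r assumed). With six clusters this does not carry over in full to the arm contrast.

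**6. Data already collected.** ECOG and age are eligibility items (section 5.A). Cancer diagnosis and treatment history are recorded at registration (section 11.B). EQ-5D, ESAS, PHQ-9 and CRA-K are marked for both arms at enrolment and 3 months (section 11.A). At 6 months that table marks them for the intervention arm only, while the overview allows consenting controls.

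**The case against.** The protocol does mention adjustment twice, the covariate list can properly sit in a statistical analysis plan, and silence is not contradiction. Section 14.B.4 also leaves out the logit link and the mixed and count models given in the overview, so it may be a summary meant to be read beside it. This has force. The missing list is not a finding, and the protocol does not say that the body overrides the synopsis. What stands is that the section headed as the statistical analysis gives a method for the primary outcome with no adjustment in it, and nothing says which description applies.

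A reader might infer more than the text supports:

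- **That the overview prescribes data-driven selection.** It gives no test, threshold or selection rule, and could mean general baseline adjustment.
- **That questionnaire outcomes are excluded from adjustment.** The overview sentence covers continuous outcomes too. The fair statement is that neither place commits to using the enrolment scores.
- **That case mix is known to differ.** How hospitals were assigned is not described and no case-mix data are given. Balance is simply not provided by the design.

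The assumed 60% and 40% risks are also well above the only event counts shown, 40/198 and 20/198 in section 6 (about 20% and 10%). ECOG 1 patients qualify only if older, so a clean 20-point risk gap by ECOG is uncertain.

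**Conclusion.** The point holds as an inconsistency with consequences. The overview and section 6 point to adjustment; sections 12.B, 12.C and 14.B.4 do not. Followed as written, section 14.B.4 yields an unadjusted comparison of non-randomised hospitals. The overview's phrase is better but leaves the covariates open.

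The size cannot be established from the documents. The 4 to 8 point bias and the 5% to 21% rejection rates rest wholly on assumed risks and imbalances. They show that a plausible imbalance would matter against a 20-point target, not that one exists. Nor should adjustment be oversold: with three hospitals per arm it cannot separate the intervention from differences between hospitals.

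**What to change.** Reconcile the overview's Statistical Analysis row with sections 12.B, 12.C and 14.B.4, so that each describes the same analysis:

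1. The primary GEE logistic model adjusts for a short set of prognostic variables already collected, fixed in advance whatever imbalance is observed. Candidates are ECOG, age, and a coarse grouping of cancer diagnosis or treatment status. Inpatient or outpatient status is not a listed baseline item and should not be assumed available.
2. The unadjusted result is reported as secondary.
3. EQ-5D, ESAS, PHQ-9 and CRA-K are each adjusted for their own enrolment score at the visits where both arms are measured. Satisfaction is left out because it has no enrolment value.
4. Residual hospital-level confounding is stated as a limitation.

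The cost is protocol wording, with no new data and no change to the sample size. The small downside is that six clusters support only a few covariates, so the list must stay short.
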